**hydrocortisone (3x/day)**

**Dexamethasone**

**+ placebo (3x/day)**

**5 days Dexa course**

**5 days Dexa course**

***Fig.2 :*** *Medium risk ALL patients will be randomised after informed consent in to two groups. One week before start of the dexamethasone course they will perform a salivary dexamethasone suppression test.*

*(Neuro-) psychological outcome parameters*

Dexamethasone induced side-effects on mood, behavior and cognition will be analyzed before and on day 5 of dexamethasone treatment with a set of validated neuropsychological assessment:

Neuropsychological tests and questionnaires developed for children and their parents were administered to assess skills in six domains in 30 minutes:

1. Behavior/mood: Strength and Difficulties Questionnaire in Dutch (SDQ-Dut)20 = primary outcome parameter.
2. Eating behavior: Dutch Eating Behavior Questionnaire (NVE-K)21
3. Sleeping disorders: Dutch version of Children’s sleep habits questionnaire22
4. Visual-spatial functions: Design copying (NEPSY II)23
5. Memory: Narrative memory and Memory for design (NEPSY II)23
6. Attention: Auditory Attention and Response Set, and Inhibition (NEPSY II)23
7. Speed: Substitution and Symbol Search (aged appropriate Wechsler; WPSSI II or WISC III)24-25.
8. Dietary diary (24 hours)
9. Daily activity: Baecke questionnaire
10. Physical activity (5 day measurement) with Philips device
11. Diary of complaints: (during to study dexamethasone courses) also contains times of medication intake

*Metabolic outcome parameters*

Data on body composition will be obtained. Height and weight will be measured. Waist-hip circumpherence and blood pressure will be measured. Fasting blood samples will be taken to measure lipid profiles (triglycerides, cholesterol, HDL, LDL), glucose and insulin levels allowing calculation of the homeostatic model assessment (HOMA)-index for evaluation of insulin sensitivity levels, lipid profiles. Some serum will be stored. The outcome parameters will be analysed separately for children above the age of six, the diagnosis of metabolic syndrome will be assessed based on IDF (international diabetes federation) criteria26.This international consensus definition is a simple and easy-to-apply clinical definition facilitating international comparison.

*Individual corticosteroid sensitivity parameters*

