For individual profiles of corticosteroid sensitivity the following data will be obtained: salivary diurnal cortisol rhythm (area under the curve), salivary very low dose (0,25 mg) dexamethasone suppression test27. This will be performed one week before start of the first study dexamethasone course and can be done at home. Salivary samples could be send to the endocrinology labarotory.

Table 2.: **Schedule Dexamethasone suppression test at home**

| **Time** | **Day 1** | **Day 2** |
| --- | --- | --- |
| awakening | Salivary sample (sober) | Salivary sample (sober) |
| 12am | Salivary sample |  |
| 4 pm | Salivary sample |  |
| 8 pm | Salivary sample |  |
| 8pm | 0.25mg dexa oral |  |

*Visits outpatient clinic*

Neuropsychological and metabolic outcome parameters will be obtained in both study courses at the first day and the fifth day of the dexamethasone course. At these days the patients will have to complete the questionnaires, fasting blood samples will be taken and neuropsychological test will be administered. Patients usually have a routine visit at the outpatient clinic the first day of each dexamethasone course. The fifth day study visit will be an extra visit for each patient.

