# STATISTICAL ANALYSIS

The particular strength of this cross over design is that the interventions under investigation are evaluated within the same patients and so eliminates between-subject variability.

To prevent carry-over effect of treatments across study periods, a wash-out period is present and with the blinded randomisation the patient will start with either placebo or trial medication in a randomised fashion.

Given that the subjects act as their own controls, the analyses are based on paired data analysis.

Primary outcome parameter is the SDQ (continuous parameters). The effectiveness of treatments is assessed by comparing the effects of placebo and trial medication on SDQ by a two-way analysis of variance, with treatment order as a between-subjects factor and treatment type as a within-subject factor.

Secondary outcome parameters are mood and behaviour questionnaires, (neuro-) cognitive tests and metabolic parameters (all continuous parameters). The effectiveness of treatments is assessed by comparing the effects of placebo and trial medication on secondary outcome parameters by a two-way analysis of variance, with treatment order as a between-subjects factor and treatment type as a within-subject factor.

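### The secondary-outcome ANOVA has no day-1 term although day 1 is measured in both courses; adjusting for it could add precision at almost no cost

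*Protocol*

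**What the plan says.** Protocol section 9 (Statistical analysis) sets one model for all secondary outcomes, that is, questionnaires, cognitive tests and metabolic parameters. Treatments are assessed by "comparing the effects of placebo and trial medication on secondary outcome parameters by a two-way analysis of variance". Only two factors are listed for this model, which is specified "with treatment order as a between-subjects factor and treatment type as a within-subject factor". No day-1 value and no time factor is named.

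Section 7.1 (Visits outpatient clinic) provides four values per child: "Neuropsychological and metabolic outcome parameters will be obtained in both study courses at the first day and the fifth day of the dexamethasone course". Earlier in section 7.1, effects on mood, behaviour and cognition "will be analyzed before and on day 5 of dexamethasone treatment with a set of validated neuropsychological assessment", but no model is named there and metabolic outcomes are not mentioned.

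The sample size subsection describes an analysis with the second measurement as outcome and the first measurement and intervention as predictors. It concerns the SDQ only.

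On carry-over, section 9 relies on the gap between courses and on the random order: "To prevent carry-over effect of treatments across study periods, a wash-out period is present and with the blinded randomisation". Section 5 gives the wash-out as 2 weeks and 2 days, which is 16 days.

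**The concern.** The protocol names a model for the secondary outcomes and leaves out a measurement it collects for most of them. Two things could follow.

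- **Precision.** In a cross-over, the day-1 value of each course can explain part of the course-to-course variation within a child. If it does, the stated model gives wider intervals than the data allow.
- **Carry-over.** Randomising the order balances the sequences but does not stop carry-over; only the wash-out can. The same tests are given at four sessions, and section 7.1 also has "Waist-hip circumpherence and blood pressure will be measured" along with weight. Such measures may not return to their starting level in 16 days. If what persists differs by the first treatment, a day-5 comparison is pulled toward no difference, and the day-1 value of course 2 is where this would show.

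**Working it through.** **The plan's own figures.** The protocol gives no power or precision figure for any secondary outcome. Its one calculation (40 children, 80% power) is for the SDQ and is not an input here.

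**Inputs from the protocol.** 50 evaluable children (section 7.5); day-1 and day-5 values in both courses (section 7.1); a correlation of 0.64 between start and finish of a course (sample size subsection, SDQ only).

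**Assumptions.** Outcomes have SD 1. r_w is the day-1/day-5 correlation within a course, and r_c is the correlation between any two values from different courses. Allocation is 1:1. k is the share of the course-1 treatment effect D still present on both day 1 and day 5 of course 2. The protocol gives no r_c, no k, and no r_w for any secondary outcome.

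**Step 1: standard errors.**
- Stated model, read as a day-5 comparison: a child's difference has variance 2(1 − r_c), so SE = √[2(1 − r_c)/50].
- Adjusted for the day-1 difference: slope b = (r_w − r_c)/(1 − r_c), and SE = √[2(1 − r_c)(1 − b²)/50].
- Within-course change: SE = √[2(1 − r_c)(2 − 2b)/50].

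Example at 0.8/0.6: b = 0.2/0.4 = 0.5. Stated √(0.8/50) = 0.126; adjusted √(0.8 × 0.75/50) = 0.110.

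**Step 2: carry-over.** Hydrocortisone-first children give D − kD and placebo-first children give D, so the day-5 contrast estimates D(1 − k/2). That is 87.5%, 75% and 50% of D at k = 0.25, 0.5 and 1. The adjusted analysis recovers 1 − (k/2)(1 − b), and within-course change recovers 100%.

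| r_w / r_c | b | SE stated | SE adjusted | SE change | Recovered at k = 0.5: stated / adjusted |
|---|---|---|---|---|---|
| 0.64 / 0.64 | 0 | 0.120 | 0.120 | 0.170 | 75% / 75% |
| 0.64 / 0.40 | 0.40 | 0.155 | 0.142 | 0.170 | 75% / 85% |
| 0.80 / 0.60 | 0.50 | 0.126 | 0.110 | 0.126 | 75% / 87.5% |
| 0.90 / 0.60 | 0.75 | 0.126 | 0.084 | 0.089 | 75% / 94% |
| 0.99 / 0.90 | 0.90 | 0.063 | 0.028 | 0.028 | 75% / 97.5% |

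A simulation with 25 + 25 children, 4,000 runs and D = 0.5 SD agrees. At 0.9/0.6 without carry-over the SEs were 0.125, 0.083 and 0.089. At 0.64/0.4 with k = 0.5 the estimates were 0.375, 0.423 and 0.499.

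**Step 3: practice or weight trend common to both sequences.** With a gain of 0.3 SD per session in every child and no treatment-dependent carry-over, the ANOVA with order returned 0.50 for a true 0.50. With 30 and 20 children per sequence it returned 0.51. A common trend is a period effect, and the order factor removes it.

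**The case against.** **The analysed value is not stated.** Section 9 does not say that the response is the raw day-5 value. A within-course change is also one value per course, would fit the same ANOVA, and sits well with the before-and-day-5 wording of section 7.1. The choice could be settled in an unseen SAP. This stands as an ambiguity, but it does not remove the point. Against a change score, the variance ratio of the adjusted analysis is (1 − b²)/(2 − 2b) = (1 + b)/2, which is never above 1. So the adjusted analysis is at least as precise in large samples on either reading.

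**The precision gain is not assured.** This stands. The cross-over already removes between-child variance. The only documented correlation is 0.64, for the SDQ, and if the cross-course correlation is similar there is no gain. The pairs 0.8/0.6 and 0.99/0.90 are illustrations.

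**A stronger reading.** A reader might infer that learned test material or weight gained in course 1 will by itself shrink a real effect. The protocol does not support that. Every child receives dexamethasone and the same tests in both courses, so the shared part is a period effect (step 3). Bias needs a hydrocortisone-specific part that lasts 16 days. A reader might also infer that the metabolic comparison will be falsely reassuring. That rests on the same undocumented carry-over, and section 2 declares the metabolic aim descriptive.

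**Conclusion.** The point holds as a modest improvement to a stated method. The secondary model names no day-1 term although the values are collected in both courses.

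The size depends on assumed correlations. With 50 evaluable children the standard error falls by about 13% at 0.8/0.6 (0.126 to 0.110 SD), by about 56% at 0.99/0.90 (0.063 to 0.028 SD), and not at all when the two correlations are equal. Apart from one degree of freedom, adjustment does not lose precision.

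Bias from carry-over is a possibility, not a demonstrated defect. It would be k/2 of the effect for a day-5 contrast, with k unknown, and day-1 adjustment would remove only part of it.

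**What to change.** In section 9, for each secondary outcome measured on day 1 and day 5:

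- Regress the within-child day-5 difference (hydrocortisone course minus placebo course) on the within-child day-1 difference, with treatment order in the model. Code order as ±1 and leave the day-1 difference uncentred, so that the intercept is the treatment effect at equal day-1 values. If the day-1 difference is centred in a balanced trial, the intercept returns to the unadjusted mean difference and the gain is lost.
- Report the within-course change (day 5 minus day 1) as a supporting analysis for very stable measures such as weight, BMI and waist-hip. It should not be the general method, because it is less precise than the day-5 contrast whenever b is below 0.5.
- Tabulate the course-2 day-1 values by treatment order, as a check on the wash-out.

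Outcomes with no day-1 value keep the stated ANOVA.

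The cost is wording, one degree of freedom per outcome, and a rule for children with a missing day-1 value. No new data are needed.

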## The end of treatment point is at the end of day 5 of the second dexamethasone study course after completion of the neuropsychological tests. There is no follow-up planned or required except for monitoring of serious adverse events.

## Sample size calculation

Power analysis was performed on the mean outcome parameter SDQ. The mean of the SDQ scale is expected to be 7,0 with a standard deviation of 6,0. In the placebo effect we expect a rise of 8 points and a correlation of 64% between measurement at start and finish of the medication period. This correlation will result in a larger power as we will perform an analysis with the second measurement as outcome and first measurement and intervention as predictors.

Iizuka et al found that children with ADHD, who have behavioural and concentration problems, have a mean SDQ score of 16, which is one standard deviation above the general population.57 After simulating five hundred datasets we found that 40 children is enough to have 80% chance of finding a significant relationship (alpha = 0.05) when the effect of the intervention is 6 points (1 SD) on the scale. Considering the probability of drop-out, a total of 50 patients will be included.

## Descriptive statistics

Descriptive statistics (N, arithmetic mean, standard deviation, minimum, median, maximum, percent coefficient of variation, and geometric mean) are presented. Missing data will be omitted from the calculation of descriptive statistics. Summaries about the sample and the measures are presented in tables and / or graphs.

## Univariate analysis

See above

## Multivariate analysis

See above

## Interim analysis (if applicable)

*Not applicable*

# ETHICAL CONSIDERATIONS

## Regulation statement

The study will be performed according to the declaration of Helsinki (09.10.2004)

and the Medical Research Involving Human Subjects Act (WMO) and the Good

Clinical Practice standard.

## Recruitment and consent

Patients will be asked to participate in the study by their pediatric oncologist and the patient information letter and informed consent form are provided. Patients will have at least 2 weeks to consider their decision, or longer if more time is needed. If patients decide not to participate in the study after being informed about the study, they will be offered to complete a voluntary questionnaire about the reason they are not participating and the type of side effects of dexamethasone they experience. This questionnaire is completely voluntary, so patients are not obliged to give a reason for not participating in the study. We will use these questionnaires to gain more information about the severity of dexamethasone side effects in the non-participating patients.

## Objection by minors or incapacitated subjects (if applicable)

The code for minors is applicable for this project (ccmo.nl).

Pediatric acute lymphoblastic leukemia is a disease in children in the age category of birth - 18 years. The study aims at reducing side effects in the treatment of this disease. Therefore, children are included in the study. In children < 12 years of age, informed consent is given by the parents/ caregivers. In children of 12 years and older, informed consent is given by the child and the parents/caregivers.

## Benefits and risks assessment, group relatedness

Given the very low risk and low to moderate patient burden of this intervention study, and that this study has the potential to have major consequences for the improvement of quality of life for all childhood ALL patients , this study is considered to have a favorable risk-benefit assessment

.

## Compensation for injury

The sponsor/investigator has a liability insurance which is in accordance with article 7, subsection 6 of the WMO.

The sponsor (also) has an insurance which is in accordance with the legal requirements in the Netherlands (Article 7 WMO and the Measure regarding Compulsory Insurance for Clinical Research in Humans of 23th June 2003). This insurance provides cover for damage to research subjects through injury or death caused by the study.

1. € 450.000,-- (i.e. four hundred and fifty thousand Euro) for death or injury for each subject who participates in the Research;
2. € 3.500.000,-- (i.e. three million five hundred thousand Euro) for death or injury for all subjects who participate in the Research;
3. € 5.000.000,-- (i.e. five million Euro) for the total damage incurred by the organisation for all damage disclosed by scientific research for the Sponsor as ‘verrichter’ in the meaning of said Act in each year of insurance coverage.

The insurance applies to the damage that becomes apparent during the study or within 4 years after the end of the study.

## Incentives (if applicable)

Not applicable

# ADMINISTRATIVE ASPECTS AND PUBLICATION

## Handling and storage of data and documents

This study will be conducted in accordance with the ethical principles that have their origin in the current Declaration of Helsinki, and will be consistent with International Conference on Harmonization Good Clinical Practice (ICH GCP) and applicable regulatory requirements.

The study will be conducted in compliance with the protocol. The protocol and any Amendments and the subject informed consent will receive Institutional Review Board (IRB)/Independent Ethics Committee (IEC) approval/favorable opinion prior to initiation of the study.

The rights, safety and well-being of the trial subjects are the most important considerations and should prevail over interests of science and society.

Study personnel involved in conducting this trial will be qualified by education, training, and experience to perform their respective task(s), and will be authorized to perform study related procedures as laid down in the delegation of authority log.

Systems with procedures that assure the quality of every aspect of the study will be implemented.

## Amendments

A ‘substantial amendment’ is defined as an amendment to the terms of the METC application, or to the protocol or any other supporting documentation, that is likely to affect to a significant degree:

- the safety or physical or mental integrity of the subjects of the trial;
- the scientific value of the trial;
- the conduct or management of the trial; or
- the quality or safety of any intervention used in the trial.

All substantial amendments will be notified to the METC and to the competent authority.

Non-substantial amendments will not be notified to the accredited METC and the competent authority, but will be recorded and filed by the sponsor.

## Annual progress report

The sponsor/investigator will submit a summary of the progress of the trial to the accredited METC once a year. Information will be provided on the date of inclusion of the first subject, numbers of subjects included and numbers of subjects that have completed the trial, serious adverse events/ serious adverse reactions, other problems, and amendments.

## End of study report

The sponsor will notify the accredited METC and the competent authority of the end of the study within a period of 90 days. The end of the study is defined as the last patient’s last visit.

In case the study is ended prematurely, the sponsor will notify the accredited METC and the competent authority within 15 days, including the reasons for the premature termination.

Within one year after the end of the study, the investigator/sponsor will submit a final study report with the results of the study, including any publications/abstracts of the study, to the accredited METC and the Competent Authority.

## Public disclosure and publication policy

This trial is registered in the Dutch trial registry. The results of this study will be disclosed unreservedly.

# MONITORING AND PATIENT SAFETY PLAN

The drugs under investigation are well characterised and are given in a physiological dose, which is known for not harming patients. Therefore we consider a minimal risk for adverse effects. We have to upgrade our risk classification to medium risk because our study group consists of vulnerable children. The monitoring frequency on site will be 2-3 times a year. Monitoring will be performed by an independent monitor of the DCOG -ECTC. Monitoring extend and other details will be described in the Monitor Manual.

# Expected outline of manuscripts:

1. In vitro and ex vivo dexamethasone sensitivity of acute lymfoblastic leukemia cells is not influenced by adding cortisol. Auteurs: [name], [name], [name], [name], [name].

2. Dexamethasone induced cerebral side-effects on mood, behaviour and cognition in children with Acute Lymphoblastic Leukemia. A Cochrane review. [name], [name], [name], [name], [name].

3. The effect of addition of cortisol to dexamethasone treatment on cognition in children with ALL. A double blind randomised trial. [name], [name], [name], [name], [name], [name], [name], [name], [name], [name]

4. The effect of combining cortisol and dexamethasone on mood and behaviour in children with ALL. A double blind randomised trial. [name], [name], [name], [name], [name], [name], [name], [name], [name]
 
5. The risk of metabolic syndrome during ALL treatment with (cortisol and) dexamethasone. [name], [name], [name], [name], [name], [name], [name], [name], [name], [name]

6. The positive predictive value of the very low dose dexamethasone suppression test, a novel in vivo diagnostic test, on severity of dexamethasone side-effects. [name], [name], [name]

